## Abstract

**Introduction:** Different sensitivity to volatile anesthetics in *Drosophila*, nematodes and mice is related to mutation of energy metabolism genes. In clinical practice, we find that the end-tidal sevoflurane concentration (ET_sevo_) differs among patients at the same depth of anesthesia, indicating that the sensitivity to sevoflurane varies among patients. However, the underlying mechanism remains unclear. The sensitivity of an anesthetic is associated with the postoperative outcomes of patients and the mechanism of action of volatile anesthetics. We therefore propose this protocol to determine whether differences in metabolite profile and genetic variations contribute to patients’ sensitivity to volatile anesthetics.

**Methods and Analysis:** This is a single-centre, prospective observational study. 720 patients undergoing abdominal surgery were included. General anesthesia was induced with inhaled sevoflurane, a bolus of sufentanil (0.2–0.4 μg/kg) and *cis*-atracurium (0.2–0.3 mg/kg). The end-tidal sevoflurane concentration (ET_sevo_) was adjusted to maintain a BIS (bispectral index) value between 40–60. The mean ET_sevo_ from 20 min after endotracheal intubation to 2 h after the beginning of surgery (steady state) was calculated for each patient. Patients were further divided into a high-sensitivity group (mean ET_sevo_ – SD) and a low-sensitivity group (mean ET_sevo_ + SD) to investigate the sensitivity to sevoflurane. Cases were paired from the high-sensitivity group (group H) and low-sensitivity group (group L) according to age, sex, body mass index (BMI), *ASA* physical status classification, vital signs, BIS, ephedrine use, sufentanildose, and *cis*-atracurium dose at anesthesia induction and steady state. Differences in metabolite levels, single nucleotide polymorphisms (SNPs) and protein-coding gene sequence variations between group H and group L will be determined through plasma metabolomics, whole-exome sequencing (WES), genome-wide association study (GWAS), and bioinformatics analyses. These results will be analysed to determine the reasons for the differential sensitivity to sevoflurane in humans.

**Ethics and Dissemination:** This prospective observational study protocol has received ethical approval from the Ethical Committee of West China Hospital of Sichuan University on May 19, 2017 (Approval No. 78). Informed consent will be obtained before patient enrolment. The results will be submitted to international peer-review journals.

**Trial Registration Number:** ChiCTR1800014327.

## Introduction

Sevoflurane is one of the most widely used volatile anesthetics, which can produce sedative, analgesic and muscle relaxing effects. Postoperative outcomes of patients may be related to the depth of anesthesia during general anesthesia (Lewis et al., 2019; Liu et al., 2019; Sieber et al., 2019). Studies have shown that excessive anesthetic depth will cause delayed emergence from anesthesia and increase the postoperative mortality of patients (Punjasawadwong et al., 2014; Short et al., 2019), while light anesthesia causes hemodynamic fluctuation, cardiovascular and cerebrovascular adverse events, intraoperative awareness, and disruption of the surgical procedure (Punjasawadwong et al., 2014). In a study including 55 patients with mild depression and major depression, ETsevo was regulated to maintain BIS values between 40 and 60. No difference was found in BIS values between the two groups during cholecystectomy, however, the ETsevo of the major depression group was significantly lower than that of the mild depression group (Erden et al., 2018). This study indicated that the sevoflurane sensitivity may be different in patients (Erden et al., 2018).

Metabolic status can be influenced by general anesthetics, and mitochondrial function may partly contribute to the mechanism of general anesthesia (Yamakage, 2014; Ramadasan-Nair et al., 2017; Zimin et al., 2018). However, the exact effects of general anesthesia on systemic metabolites in humans remain unclear, which may be important for postoperative outcomes. It is widely known that general anesthetics can affect some important metabolism and metabolic connectivity (Alkire et al., 2008; Chen et al., 2019). Sevoflurane inhibits insulin secretion and is associated with hyperglycaemia (Li et al., 2014; Hoyer et al., 2018). However, the exact modulation of systemic metabolism by general anesthetics in humans has not been clearly illustrated. Glutamate is one of the main excitatory neurotransmitters in the brain and is involved in the mechanism of action of inhaled anesthetics (Aksenov et al., 2019). Glutamate transporter 3 (EAAT3) can absorb extracellular glutamate. EAAT3 gene knockout mice exhibit significantly increased sensitivity to isoflurane, indicating that glutamate metabolism may be related to the sensitivity to inhaled anesthetics (Lee et al., 2010).

Mutations of several genes are associated with altered sensitivity to volatile anesthetics in fruit flies, nematodes and mice (Campbell et al., 2009; Nagasaka et al., 2017; Awal et al., 2020). The product of Gas-1 gene is a subunit of mitochondrial complex I (Kayser et al., 2004). The sensitivity to fluorine significantly increased in nematodes with Gas-1 gene mutation, probably due to the inhibition of mitochondrial respiratory function (Kayser et al., 2004). The literature showed that the MAC value and EC50 for isoflurane anesthesia were decreased in shank-3 mutant mice, which may be associated with the decreased expression of NR1 and PSD95 genes (Li et al., 2017).

This study aims to determine differential metabolites, SNPs and genes related to sevoflurane sensitivity among patients through plasma metabolomics, WES, GWAS and bioinformatics. Therefore, this study may identify potential markers of sevoflurane sensitivity for further studies.

## Methods and Analysis

Detailed methods with regards to the intervention and analysis are available in the full pilot study protocol included with this summary.

**FIGURE 1 F1:**
[figure not shown]
Flow diagram of the study.

The mean ETsevo from 20 min after endotracheal intubation to 2 h after starting surgery (steady state) was calculated in all patients. The data with normal distribution was present with mean ± standard deviation (SD). High-sensitivity was defined by an ET_sevo_ at least 1 standard deviation lower than the mean. Low-sensitivity was defined by an ET_sevo_at least 1 standard deviation higher than the mean. We have paired patients from the high-sensitivity group (group H) and low-sensitivity group (group L) according to age, sex, operation method (laparotomy/laparoscopic surgery), body mass index (BMI), *ASA* physical status classification, vital signs, end-tidal partial pressure of carbon dioxide (P_ET_CO_2_), BIS values, ephedrine use, and the sufentanil and *cis*-atracurium doses at anesthesia induction and steady state. We performed follow up to determine the occurrence of intraoperative awareness, postoperative nausea and vomiting in patients at the post-anesthesia care unit, and at postoperative day 1 and 3.

The plasma collected before anesthesia induction and at 2 h after starting surgery in group H and group L was labelled with group H-before, H-after, L-before and L-after, respectively. Quality control of all plasma samples were implemented. The stability of the instrument and the acquired signal were monitored in real-time to ensure the quality of process (process quality control). The chromatography mass spectrometry may be affected by the aging circuit board, humidity, temperature, vibration and other factors, which will cause the fluctuation of acquired signal. Therefore, data processing is required to obtain high quality data (data quality control).

LC-MS/MS analysis will be performed using an UHPLC system (1,290, Agilent Technologies) coupled to a Q Exactive Orbitrap high-resolution mass spectrometer. The mobile phase composition was divided into positive and negative ionic modes. Each mode included mobile phase A and mobile phase B. Mobile phase setting: 0.1% formic acid and 5 mmol/L ammonium acetate were the mobile phases of positive and negative ion mode A; and acetonitrile were the mobile phases of positive and negative ion mode B. ProteoWizard software was used to transform the original data into mzML format. XCMS software was used to correct peak recognition, peak extraction, peak alignment and peak integration. OSI-SMMS software was used to identify the differential metabolites (Version 1.0, Dalian Dataso Information Technology Co., LTD.).

The differential metabolites were mapped to KEGG metabolic pathways by enrichment analysis. Several differential metabolites will be selected according to the aims of the study. Multiple linear regression analysis will be conducted using MetaboAnalyst 4.0 software to explore the correlation between the level of differential metabolites and ET_sevo_ and to calculate the area under the concentration-time curve of ET_sevo_ (AUC_sevo_).

Genomic DNA in group H and group L will be extracted and subjected to sample quality control. The OD value of nucleic acid was detected by nanodrop microspectro photometer. A260/A280 ratio <1.8 indicates protein pollution. A260/A280 ratio >2.0 indicates RNA pollution. The intact genomic DNA was present as a single band after agarose gel electrophoresis. Genomic DNA was processed after quality control, including ultrasonic fragmentation, DNA end repair and sequencing adapter ligation at both ends. Exons will be captured on the liquid phase platform. After capturing fragments using PCR amplification, sequencing will be performed using the Illumina HiSeq 4,000 platform. The raw data will be analysed for quality control. High quality clean reads were obtained by strict filtration. The steps of filtering are: 1) remove adapter and retain remaining reads; 2) remove reads containing more than 10% of N; 3) remove low-quality reads (the number of bases with mass value Q ≤ 20 accounts for more than 50% of the whole read). The comparison software BWA (0.7.15) and MEM algorithm were used to compare the filtered reads to the reference genome. Then, the SAM format comparison results were obtained, and the SAM tool was used to output the comparison results as BAM format files. Finally, Picard 1.129 software (Mark Duplicates) was used to mark duplicate reads, and the depth and coverage of labelled reads were calculated. Allele frequency screening was used to find SNPs. The variations in SNPs will be analysed using comparative statistics with reference genomes. ANNOVAR software will be used for advanced annotation of detected variations. Then GWAS will be used to investigate the correlation between SNPs and ETsevo in group H and group L. After different models of GWAS analysis was completed, the distribution of actual *p*-values and theoretical *p*-values under different models will be compared by Q-Q diagram to determine the optimal model. Bonferroni multiple test correction method will be used to determine the significance threshold of *p* value and screen the SNPs in the region of strongest correlation for subsequent analysis. The results of GWAS analysis will be presented in the form of Manhattan Plot. The screening criteria for SNPs includes: 1) *p* < 0.001; 2) non-synonymous mutation; 3) from the exon region; 4) mutant genes with known functions; and 5) the difference in SNP mutation frequency between group H and group L was more than 5%.

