### Interventions

Bradycardia is defined as a HR of <60 beats per minute. If HR is below 50 beats per minute with hypotension, atropine or ephedrine will be administered. Tachycardia is defined as a HR > 100 beats per minute. If the depth of anesthesia and the degree of analgesia are sufficient and a HR > 90 beats per minute is observed, esmolol will be administered. Hypotension is defined as systolic pressure <90 mmHg or diastolic pressure <50 mmHg. Hypertension is defined as over 20% of the baseline blood pressure. If hypotension or hypertension occurs, metaraminol, urapidil hydrochloride or nicardipine hydrochloride will be administered.

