### Outcomes

The primary outcome is the incidence of high sensitivity to sevoflurane in patients. Secondary outcomes include the following:1) The average ETsevo at stable state;2) Tracheal extubation time;3) Incidence of intraoperative awareness;4) The use of vasoactive drugs;5) Incidence of postoperative nausea and vomiting.

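### Groups H and L are paired on ephedrine use and vital signs, so comparing vasoactive drug use in the pairs would be pulled towards no difference; analyse it before matching

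*Protocol article*

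**What the plan says.** The Study Design section defines the exposure first: "The mean ETsevo from 20 min after endotracheal intubation to 2 h after starting surgery (steady state) was calculated in all patients". The groups are cut from that quantity: "High-sensitivity was defined by an ET_sevo_ at least 1 standard deviation lower than the mean", with low sensitivity defined symmetrically above the mean. H and L are the only comparison groups the article defines.

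The two groups are then paired. The Study Design list includes "vital signs, end-tidal partial pressure of carbon dioxide" and "BIS values, ephedrine use, and the sufentanil and *cis*-atracurium doses at anesthesia induction and steady state". The Abstract repeats the main items: "vital signs, BIS, ephedrine use, sufentanildose, and *cis*-atracurium dose at anesthesia induction and steady state".

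The Outcomes section names "The average ETsevo at stable state" as the first secondary outcome and "The use of vasoactive drugs" as the fourth. It gives no analysis set for any of them. The Statistical Methods section says only that groups are compared by t-test, Mann-Whitney or chi-squared test.

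The Interventions section ties vasoactive drugs to haemodynamics: "If HR is below 50 beats per minute with hypotension, atropine or ephedrine will be administered". It makes esmolol depend on heart rate, and metaraminol, urapidil and nicardipine depend on blood pressure. The Study Design section also says that sevoflurane itself was adjusted according to vital signs.

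**The concern.** One component of a secondary outcome (ephedrine) is a matching variable. The triggers for the remaining components (heart rate and blood pressure) are matching variables too. A comparison within such pairs cannot show whether sensitive patients need more or less vasoactive support, because the pairing has already balanced much of what is being measured. A null result could then be read as evidence that sensitivity is unrelated to haemodynamic support, when it would mainly reflect how the pairs were chosen.

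A smaller, related point concerns mean end-tidal sevoflurane. It defines H and L, so a test of it between those groups carries no information.

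**Working it through.** **No planning figure applies.** The article gives no expected rate of vasoactive use and no target number of pairs, so there is nothing of its own to reproduce on this point. The overlap follows from setting its lists side by side; the size has to be assumed.

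**Step 1: the overlap.**
- Matched: ephedrine use and vital signs (Study Design; Abstract).
- Outcome: use of vasoactive drugs (Outcomes).
- Ephedrine is a vasoactive drug, and the other agents are given for heart rate or blood pressure (Interventions).

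The phrase about induction and steady state at the end of the matching list could apply to the drug doses alone. That changes little, because ephedrine use and any vital sign recorded after induction still follow the start of sevoflurane.

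**Step 2: what exact matching on ephedrine does.** Let E be ephedrine use, O use of any other vasoactive drug, and V = E or O. In pairs matched on E, P(E) is the same in H and L, so:
- difference in E = 0, whatever the truth;
- difference in V = P(E = 0) × [P(O | E = 0, H) − P(O | E = 0, L)].

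Only patients without ephedrine can contribute, and only through the other drugs. If blood pressure and heart rate are also matched, the bracket shrinks too, because they trigger O.

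**Step 3: a hand example (assumed rates).** Take ephedrine 45% in H and 30% in L, with other drugs 10% in both and independent of ephedrine. Unmatched, the difference in V is (1 − 0.10) × (0.45 − 0.30) = 0.135, or 13.5 points. Matched on ephedrine, it is 0. The exact zero for V depends on other-drug use being equal in the two groups.

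**Step 4: simulation without that equality.** All effect sizes are assumptions.
- 720 patients, 400 repeats; s is standardised end-tidal sevoflurane; H is s at least 1 SD below the mean, L at least 1 SD above. A normal tail gives 0.1587 × 720 = 114 per group.
- Blood pressure = 0.5 × b × s + standard normal noise, with b = 0.3 (weak), 0.6 (medium) or 1.0 (strong).
- logit P(ephedrine) = −0.6 − blood pressure; logit P(other) = −1.6 − blood pressure.
- Matching is exact on ephedrine, then also on blood pressure within 0.2 (noise SD = 1).

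H minus L difference in any vasoactive use, in percentage points:

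| Link | Unmatched | Ephedrine matched | Ephedrine and blood pressure matched |
|---|---|---|---|
| Weak | 10.5 | 3.1 | 0.2 |
| Medium | 20.3 | 5.7 | −0.2 |
| Strong | 33.0 | 10.2 | 0.4 |

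The ephedrine difference itself was 8.9, 17.7 and 28.4 points unmatched, and exactly 0 after matching in every case.

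One simplification should be noted. The simulation treats the other drugs as given for low pressure. The plan's list also includes agents for high pressure or fast heart rate, which could offset the unmatched composite. Matching on the triggers would still pull each component towards no difference.

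**Step 5: mean end-tidal sevoflurane.** Every H patient lies at least 1 SD below the mean and every L patient at least 1 SD above, so any H–L pair differs by at least 1 + 1 = 2 SD by definition.

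**Step 6: why all 720 patients are the better set.** Suppose a continuous outcome correlates 0.10 with end-tidal sevoflurane (assumed).
- All 720: atanh(0.10) × √717 = 2.69, so power is Φ(2.69 − 1.96) = 77%.
- Unmatched H v L, 114 each: under normality the group means lie 2 × 0.2420 / 0.1587 = 3.05 SD apart, so d = 3.05 × 0.10 / √0.99 = 0.307. Then 0.307 × √(114/2) = 2.31, and power is Φ(2.31 − 1.96) = 64%.

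This compares a continuous predictor with extreme groups. It does not measure the effect of matching.

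**The case against.** The strongest reply is that the article never says the secondary outcomes are compared in the pairs. The primary outcome is a whole-cohort incidence, mean end-tidal sevoflurane was calculated in all patients, and the Objectives tie H v L only to metabolites, SNPs and genes. The article also refers to a fuller protocol that is not shown. If vasoactive use is compared in unmatched H and L, the pairing does not touch it. This stands, and it makes the point conditional. It does not remove it: H and L are the only groups defined, and nothing in the article exempts this outcome from the pairing.

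A reader might go further and infer that matching on intra-operative ephedrine and vital signs can only remove real signal from the genetic and pre-induction metabolite comparisons, since DNA and baseline plasma precede both. The documents do not support that. Sevoflurane was adjusted according to vital signs, so a patient kept on a low concentration because of low pressure may be labelled sensitive without being so, and matching on vital signs can reduce that misclassification. The timing argument would also rule out BIS and opioid dose, which are equally intra-operative. For the 2-hour plasma, drawn after any ephedrine given up to then, balance on ephedrine is a defensible choice.

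A reader might also want H and L redefined from residuals after regression on covariates. Pairing is reported as done, and that change would create a second definition of high sensitivity beside the one behind the primary outcome. It is not recommended here.

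**Conclusion.** The point holds conditionally. If use of vasoactive drugs is compared between paired H and L patients, the ephedrine part is null by construction and the rest is pulled towards no difference. How far depends on links that the documents do not quantify: under the assumed range, 10.5 to 33.0 points unmatched become 3.1 to 10.2 with ephedrine matched, and about 0 with blood pressure matched as well. That low end-tidal sevoflurane goes with lower pressure and more pressor use is an inference, in keeping with the Study Design and Interventions text but not stated there.

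A reader might infer that two of the five secondary outcomes are already decided by design. The article does not say so: mean end-tidal sevoflurane can be read as a cohort description, and vasoactive use is affected only in the paired set. The primary incidence outcome is untouched.

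**What to change.** - **Clinical secondary outcomes.** State that vasoactive drug use, extubation time and postoperative nausea and vomiting are analysed before matching. Preferably use all 720 patients, with steady-state end-tidal sevoflurane as a continuous predictor (logistic regression for the binary outcomes), adjusted for age, sex, BMI, ASA class, operation method, BIS and opioid dose. At the least, compare the unmatched H and L groups. Do not adjust for ephedrine use or intra-operative vital signs.
- **Mean end-tidal sevoflurane.** Report it descriptively, not as an H v L test.
- **Omics work.** Keep the existing pairs. Add a sensitivity analysis of the genetic and pre-induction metabolite comparisons that does not match on ephedrine use or vital signs.

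The cost is a few sentences in the plan and some extra regression on data already collected; no patient contact or clinical conduct changes. The clinical outcomes will be reported in a different set from the omics pairs, which the report should explain. If only paired patients are assayed, the sensitivity analysis may be limited to the assayed patients or need further assays.

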### Statistical Methods

Statistical analyses will be performed using SPSS (Version 22.0, IBM Corp., Armonk, NY, United States). Normally distributed data will be presented as the mean ± SD, whereas non-normally distributed data will be presented as the median and interquartile range. Analysis of variance will be used for continuous variables. Categorical data will be presented as numbers and compared using the chi-squared test. Groups will be compared using Student’s *t*-test (normally distributed data) or the Mann-Whitney *U* test (nonnormally distributed data). After identification of differential metabolites and multivariate statistical analysis, metabolites with significant differences between groups will be screened by variable importance in projection (VIP) of model variables with orthogonal partial least squares discriminant analysis (OPLS-DA) and the *p* value of the *t* test for univariate statistical analysis. Metabolites with *p* < 0.05 and VIP ≥1 were considered differential metabolites between comparisons. To identify correlations between metabolite levels and the amount of sevoflurane exposure, multivariate linear regression or Pearson’s correlation analysis will be performed using MetaboAnalyst 4.0 software.

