## Discussion

The sensitivity to volatile anesthetics may be related to postoperative outcomes of patients and the action mechanism of volatile anesthetics. Sevoflurane is widely used for various surgeries. However, very few studies described differential sensitivity to sevoflurane among patients. We previously found that the genes associated with mitochondrial energy metabolism were involved in sensitivity to sevoflurane in *Drosophila*, and changes in these genes can cause changes in the levels of metabolites in the body (Liu et al., 2009). In clinic, we found that the end-tidal sevoflurane concentration (ETsevo) was different among patients at the same depth of anesthesia. However, the precise underlying mechanism remains unclear. In addition, genetic variations in *Drosophila*, nematodes and mice affect their sensitivity to volatile anesthetics (Morgan and Sedensky, 1994; Kayser et al., 1999; Falk et al., 2006; Borghese et al., 2012; Hu et al., 2012; Zalucki et al., 2015). Therefore, changes in metabolites and genetic variations may be involved in anesthetic efficacy (Olufs et al., 2018). However, no current study has demonstrated whether changes in metabolites and genetic variations are associated with anesthesia sensitivity in patients.

This study is a prospective observational study to identify potential metabolites, SNPs and genes related to sevoflurane sensitivity. Cases with different levels of sevoflurane sensitivity will be screened according to the ETsevo for maintaining the target depth of anesthesia. After pairing cases of high-sensitivity and low-sensitivity to sevoflurane, differential metabolites, SNPs and genes may be identified through plasma metabolomics, whole-exome sequencing (WES), GWAS and bioinformatics. Therefore, this study will identify potential markers of sevoflurane sensitivity for further studies.

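### Metabolites are screened on groups cut from ETsevo, shortlisted by an open criterion, and then regressed on ETsevo, so the regression p values have no valid error rate

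*Protocol article*

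**What the plan says.** The Study Design section, in the metabolomics text after Figure 1, gives a sequence. Differential metabolites are mapped to KEGG pathways; then "Several differential metabolites will be selected according to the aims of the study"; then multiple linear regression is used "to explore the correlation between the level of differential metabolites and ET_sevo".

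Statistical Methods defines the screen: "Metabolites with *p* < 0.05 and VIP ≥1 were considered differential metabolites between comparisons". No multiplicity adjustment is stated for it. The same section words the later analysis more broadly: "To identify correlations between metabolite levels and the amount of sevoflurane exposure, multivariate linear regression or Pearson’s correlation analysis will be performed".

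The groups being compared come from the regression outcome. In Study Design, "High-sensitivity was defined by an ET_sevo_ at least 1 standard deviation lower than the mean", and low sensitivity is an ETsevo "at least 1 standard deviation higher than the mean".

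For the SNPs, by contrast, the article lists five screening criteria and says that a "Bonferroni multiple test correction method will be used to determine the significance threshold of *p* value".

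**The concern.** Two features of this sequence matter.

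- **The shortlist rule does not bind.** It refers to the study's aims, but the second aim under Objectives is simply to find metabolites that differ between H and L. Every differential metabolite meets that aim, so the rule excludes none of them. The choice is made once the group results and the pathway map are known.
- **The regression reuses the screening information.** A metabolite becomes differential because its level differs between low-ETsevo and high-ETsevo patients. Regressing it on ETsevo in those patients largely repeats the same test, and its p value is then read as if it were a first look.

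At stake is how the metabolite results are read. A significant correlation with ETsevo would look like a second, graded line of evidence for a candidate marker, when most chance findings from the screen would also show it.

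**Working it through.** The article gives no error rate, power or sample size for these correlations, so there is no stated figure to reproduce.

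**Inputs from the article:** 720 patients; H and L as the 1-SD tails of ETsevo; screen at unadjusted p < 0.05.

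**Assumptions:** normal ETsevo (about 114 patients expected in each tail, 720 × 0.1587); 30, 60 or 100 H-L pairs; 200, 500 or 1000 independent metabolite features; no metabolite related to ETsevo. The matching and the VIP condition are not modelled.

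**Step 1, the screen.** Expected false differential metabolites = 0.05 × number of features: 10 from 200, 25 from 500, 50 from 1000.

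**Step 2, overlap of the two tests.** For a standard normal ETsevo beyond 1 SD on either side:

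- mean distance from the centre = φ(1)/Φ(−1) = 0.2420/0.1587 = 1.525
- mean square = 1 + 1.525 = 2.525, so SD = 1.589
- correlation between group label and ETsevo = 1.525/1.589 = 0.96

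In large samples the group-comparison and regression statistics therefore correlate at about 0.96 under the null. For two standard normal statistics with that correlation, the probability that the second exceeds 1.96 in absolute value, given that the first does, is 0.0369/0.05 = 0.74.

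**Step 3, null simulation (300 runs per setting).** The screen is applied and ETsevo is then correlated with the metabolites:

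| Second step | Share at p < 0.05 |
|---|---|
| No screening | 5% |
| Every screened metabolite, same patients | 74–75% |
| Five arbitrary screened metabolites, same patients | 72–75% |
| Five with the smallest regression p values, same patients | 96–100% |
| Coefficients in one five-metabolite regression, same patients | 36–51% |
| Five screened metabolites, in patients not used for the screen | 5–6% |

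The chance of at least one significant result among five arbitrary screened metabolites was 0.99–1.00. For five independent tests not preceded by the screen it is 1 − 0.95^5 = 0.226.

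**Step 4, candidate remedies under the same null.** Benjamini-Hochberg applied only to the screened set still gave at least one false discovery in 85–96% of runs. Applied to all measured metabolites, or with five metabolites named beforehand, the nominal rate was restored.

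**The case against.** The strongest objection is that this is an exploratory step in a condensed article. The regression is introduced as exploration, the output is candidate markers for later work, the lack of validation is a stated limitation, and the article refers to a fuller protocol that is not shown. A shortlist criterion could be set out there. This stands as a limit on severity: nothing here touches the primary outcome or the listed secondary outcomes. It does not remove the point, because the sequence the article does state yields invalid p values however the shortlist is specified.

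Three stronger readings are tempting but not supported:

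- **Only the shortlisted metabolites are regressed and reported.** This is a natural reading of consecutive sentences, but it is not stated. The regression sentence says differential metabolites, Statistical Methods says metabolite levels, and nothing says that the others go unreported.
- **The choice will favour energy or glutamate metabolism.** The Discussion recalls earlier *Drosophila* work in which "the genes associated with mitochondrial energy metabolism were involved in sensitivity to sevoflurane", and the Introduction discusses glutamate. These are background; the aims under Objectives name no pathway.
- **Discretion is what destroys the error rate.** The simulation shows otherwise: the rate is 74–75% with no choice at all. Choice raises it further only if the picks follow the observed p values, and the article describes choosing by aims.

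**Conclusion.** The point holds in this form: the selection rule is open, and the regression p values for H/L-screened metabolites in the same patients have no valid error rate. Under a true null about three quarters of them reach p < 0.05 instead of one in twenty, and the main cause is circularity.

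The figure rests on normal ETsevo, independent features, a t-test screen without the VIP condition, and unmodelled matching. It varies little over the assumed numbers of pairs and features. It applies to metabolites screened on H versus L and regressed in those patients, which is how the article sets out the metabolomics; a metabolite called differential only from a before-versus-after comparison would not carry this circularity.

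The consequence is confined to how the exploratory correlations may be reported. It is worth correcting before the results are written up.

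**What to change.** Replace the selection sentence with a rule under which correlations with ETsevo are tested in one of two ways:

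- (a) for all measured metabolites, with Benjamini-Hochberg control over that full set, not over the metabolites that passed the screen; or
- (b) for a subset named before the H/L labels are joined to the metabolite data, with adjustment over that subset.

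Report results for every differential metabolite. Label any correlation of screened metabolites in the same H/L patients as descriptive, giving estimates without p-value claims. Biological interest can still guide the discussion. If the labels have already been joined, option (b) is closed and (a) remains.

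The cost is one supplementary table and fewer nominally significant correlations. No new data are needed.
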